## Abstract

**Background:**

Spinal cord injury (SCI) creates a complex pathology that can lead to an increase in sedentary behaviours and deleterious changes in body composition. Consequently, individuals with SCI are at increased risk of developing cardiovascular disease and type-2 diabetes mellitus. While the role of physical activity on the reduction of chronic disease risk is well documented in non-disabled individuals the evidence is less conclusive for persons with SCI. The aim of this methodological paper is to outline the design of a study that will assess the role of a home-based exercise intervention on biomarkers of metabolic and cardiovascular health in persons with SCI: the HOMEX-SCI study.

**Methods/design:**

Eligible participants will be inactive (physical activity level ≤1.60) individuals, with a chronic (more than 1 year) spinal cord lesion between the second thoracic and the fifth lumbar vertebrae, and aged between 18 and 65 years. Following baseline laboratory testing and lifestyle monitoring, participants will be randomly allocated to a control (CON) group or a 6-week home-based exercise intervention (INT) group. The INT consists of 45 minutes of moderate-intensity (60–65 % peak oxygen uptake) arm-crank exercise four times per week. Participants assigned to the CON group will be asked to maintain their normal lifestyle. The main outcomes of this study (biomarkers of metabolic and cardiovascular health) are obtained from venous blood samples, collected in the fasted and postprandial state. Eight other measurement categories will be assessed: (1) body composition, (2) physical activity, (3) energy intake, (4) measures of health and wellbeing, (5) resting metabolic rate, heart rate and blood pressure, (6) aerobic capacity, (7) immune function, and (8) adipose tissue gene expression.

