### Objectives

The primary objective of the HOMEX-SCI study is to assess the impact of a 6-week home-based moderate-intensity arm-crank exercise intervention on markers of metabolic and cardiovascular health in inactive individuals with chronic SCI. Little is known about the impact of a moderate- to vigorous-intensity exercise intervention on messenger ribonucleic acid (mRNA) expression of adipose tissue, which is surprising considering that it is a major site for energy storage. To our knowledge, adipose tissue biology has never been studied in a cohort of individuals with SCI. Thus, a secondary objective is to investigate at baseline, and following intervention, the expression of genes within adipose tissue that are associated with a variety of biological processes such as energy homeostasis, glucose metabolism, lipid metabolism and inflammatory responses. Other objectives include: characterising aspects of adaptive immune function pre and post intervention, quantifying changes in body composition, aerobic capacity, dietary and physical activity behaviours and various constructs of health and wellbeing. The exercise intervention group’s responses, for all outcome measures over 6 weeks, will be compared to a control group.

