#### Blood measurements

The metabolic and cardiovascular health, along with immune function variables measured are shown in Table 1. Besides the haematological profile which is measured immediately during the main trial day, these variables will be quantified during a batch analysis once the final participant has completed the study. In order to simplify data analysis and facilitate the interpretation of a complex data set [78, 79], serial measurements of glucose and insulin responses to the OGTT at baseline and follow-up will be converted into simple summary statistics [80], such as incremental area under the curve (iAUC) [81] and insulin sensitivity index (ISI_Matsuda_) [82]. The Homeostasis Model Assessment (HOMA) calculator, incorporating the updated HOMA-2 model [83], will be used to derive fasting estimates of pancreatic β-cell function, insulin resistance and sensitivity.

**Table 1 Tab1:** Metabolic health, cardiovascular disease risk and immune function variables

Haematological profile	Analytical techniques
Red blood cell, white blood cell, neutrophil, lymphocyte, monocyte and platelet counts, haemoglobin concentrations, haematocrit and haematic indices	Automated haematology system (SF-300, Sysmex Ltd., Milton Keynes, UK)
Biochemical variables	Analytical techniques
Triglycerides, total cholesterol, NEFA, HDL-C, LDL-C, glucose	Automated analyser (Randox RX Daytona, Randox Laboratories, Co. Antrim, UK), in accordance with manufacturer’s instructions using commercially available immunoassays (Randox Laboratories, Co. Antrim, UK).
Insulin	ELISA (Mercodia AB, Uppsala, Sweden)
Adipokines	Analytical techniques
Leptin and adiponectin	ELISA (Quantikine HS, R&D Systems Inc., Abingdon, UK)
Inflammation	Analytical techniques
IL-6	ELISA (Quantikine HS, R&D Systems Inc., Abingdon, UK)
CRP	Automated analyser (Randox RX Daytona, Randox Laboratories, Co. Antrim, UK),
Immune function	Analytical techniques
T cell anti-viral IFN-γ production	Human IFN-γ ELISpot^BASIC^ (Mabtech, Nacka Strand, Sweden)

*CRP* C-reactive protein, *ELISA* enzyme-linked immunosorbent assay, *ELISpot* enzyme-linked immunospot, *HDL-C* high-density lipoprotein cholesterol, *IFN-γ* interferon gamma, *IL-6* interleukin-6, *LDL-C* low-density lipoprotein cholesterol, *NEFA* non-esterified fatty acid

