### Statistical analysis

Changes in key outcome variables within and between trials will be analysed with two-way (group [INT, CON] × day [baseline, follow-up]) and three-way (group [INT, CON] × day [baseline, follow-up × time]) mixed-model analysis of variance (ANOVA). Where significant interactions are observed, multiple *t* tests will determine the location of variance both between treatments at each time point and between time points within each treatment relative to baseline. Both methods will be subjected to a Holm-Bonferroni stepwise adjustment [97]. Standardised effect sizes (Cohen’s *d*) will also be calculated for all variables. Based upon the magnitude of correlation between trials, thresholds of >0.2 (small), >0.5 (moderate) and >0.8 (large) have been suggested [98]. This provides an interpretation of the size of the effects in our outcome measures when using a parallel-group’s study design. Magnitude-based inferences will also be calculated to examine the impact of exercise on all variables of interest.

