#### Power calculation and sample size

The sample size was calculated using statistical software (G*Power 3.1.5) on the main outcome measure, fasting serum insulin concentration. This calculation was based on data from a hand-cycling training group, which reported an improvement of −14.3 ± 12.7 pmol l^−1^ [59] in fasting insulin over 16 weeks. Based upon these data (Cohen’s *d* = −1.1) it was estimated that nine participants are required to detect a statistically significant change in insulin sensitivity in the INT group. The power was 0.8 and the alpha was set at 0.05. As a 2:1 ratio is to be adopted, a computer programme (www.statstodo.com/SSizUnequal_Pgm.php) was used to calculate sample size adjustments for two groups with unequal size, to account for any consequences of unequal allocation on statistical power [99]. Also, taking into account an expected drop-out rate of approximately 15 %, we aim to recruit at least 24 (INT: 16, CON: 8) participants with chronic paraplegia.

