## Discussion

To our knowledge, this will be the first study to simultaneously evaluate the efficacy of a home-based arm-crank ergometry exercise intervention and explore the biological mechanisms of action in persons with chronic SCI. Considering the aforementioned barriers to engage in PA, a convenient and accessible form of exercise is necessary to maximise exercise compliance in this population. A 16-week laboratory-based RCT [59], which experienced large drop-out rates, has recently advocated that researchers should consider how to make exercise interventions more feasible to individuals with SCI. Home-based arm-crank ergometer exercise has been examined in other hard-to-reach groups (polio patients) [100] and will overcome transportation barriers and the lack of accessible exercise equipment. Changes in outcome measures with increased PA, achieved through enhanced compliance, may indicate that home-based arm-crank exercise has the potential to be used as a more long-term behavioural strategy to improve clinical outcomes and quality of life in persons with SCI.

Various exercise intervention protocols have been employed for individuals with SCI previously, including arm-crank ergometry [101], functional electrical stimulation (FES) [102] or wheelchair propulsion [103] ranging from between 5 to 57 weeks in duration. The frequency of exercise in these studies was typically between two and three sessions per week lasting 30 to 60 minutes per session. We settled on the proposed intervention of 6 weeks of arm-crank exercise, 4 × 45 minutes per week, in order to provide a considerable exercise stimulus. Over this time-course we expect to see improvements in our primary outcome measure of metabolic control, irrespective of weight loss (which may be negligible as a result of a compensatory increase in energy intake) [104].

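### The article gives four different accounts of its main or primary outcome, and the stated Holm adjustment most naturally does not cover a family of biomarkers

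*Protocol article*

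**What the plan says.** Four sections of the protocol article describe the main or primary outcome.

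- **Abstract, Methods/design:** "The main outcomes of this study (biomarkers of metabolic and cardiovascular health) are obtained from venous blood samples". The sentence goes on to say that samples are taken both fasted and after the glucose load.
- **Objectives:** the primary objective is the effect of the intervention "on markers of metabolic and cardiovascular health in inactive individuals with chronic SCI".
- **Power calculation and sample size:** the calculation was done "on the main outcome measure, fasting serum insulin concentration". Two sentences later the target is different: "nine participants are required to detect a statistically significant change in insulin sensitivity in the INT group".
- **Discussion:** "we expect to see improvements in our primary outcome measure of metabolic control", with no variable named.

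The Statistical analysis section plans mixed-model ANOVAs of group by day (and by time within the day) for key outcome variables, which it does not list. After a significant interaction, t tests compare the groups at each time point and compare time points within each group. Then: "Both methods will be subjected to a Holm-Bonferroni stepwise adjustment".

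**The concern.** A reader cannot tell from the article which result decides the primary objective. Fasting insulin is one variable. Insulin sensitivity is another, which the Blood measurements section derives separately from the glucose tolerance test and from HOMA-2. The biomarkers of metabolic and cardiovascular health are a set, and metabolic control is a domain.

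This matters because only the first of these was sized. If the set is taken as primary, each biomarker has its own interaction test at 5%, and nothing in the text ties those tests together. A favourable result on an outcome for which the trial was not sized could then be presented as meeting the primary objective. The authors hope that the findings may help to shape activity guidance for this population, so the status of each result should be clear before the results are known.

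**Working it through.** **1. The plan's own figures.** Inputs from the sample size section: change −14.3, SD 12.7, d = −1.1, alpha 0.05, power 0.8, 2:1 allocation, about 15% drop-out.

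- Ratio: 14.3 / 12.7 = 1.126, given as 1.1.
- Paired t test, two-sided 0.05, noncentrality d√n with n − 1 degrees of freedom and d = 1.1: power is 0.761 at n = 8 and 0.823 at n = 9. The nine is reproduced.
- Two arms of nine give 18. The factor for 2:1 allocation is (1 + k)² / (4k) = 9/8 at k = 2, so 18 × 9/8 = 20.25.
- Drop-out: 20.25 / 0.85 = 23.8, rounded up to 24. The total is reproduced.

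The stated size is therefore consistent with one outcome tested at an undivided 0.05.

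**2. How many outcomes the plural reading covers.** Table 1 lists "Triglycerides, total cholesterol, NEFA, HDL-C, LDL-C, glucose", which is six. Insulin, leptin, adiponectin, IL-6 and CRP bring the count to 11. Haematology and the T cell assay are left out.

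**3. What the Holm step covers.** The sentence about both methods comes directly after the one describing between-group and within-group t tests. Its natural reference is those two sets of tests, within a variable whose interaction was already significant. Even if the ANOVAs were meant, no family of outcomes is named.

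**4. Family-wise error under each reading.**

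- Fasting insulin alone: one test, 5%.
- Eleven independent tests at 5%: 1 − 0.95^11 = 0.431.
- Eleven correlated tests: the documents give no correlations, so these are assumed. Equicorrelated normal statistics were simulated as √ρ·z₀ + √(1 − ρ)·zⱼ, with 400,000 draws, counting any |z| > 1.96.

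| Assumed ρ | Chance of at least one false positive |
|---|---|
| 0 (formula) | 43.1% |
| 0.3 | 37.5% |
| 0.5 | 30.4% |
| 0.8 | 18.1% |

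For comparison, the first Holm step over 11 outcomes would need 0.05 / 11 = 0.0045, against the 0.05 used for the sample size.

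**The case against.** The best defence is that the article does name one outcome in the section where it has most force. The sample size section uses the singular, and the figures reproduce from it. The other statements can be read as looser prose. The abstract contrasts blood biomarkers with eight other measurement categories, an objective is usually broader than an endpoint, and the Discussion names a domain that includes fasting insulin. Error control across outcomes is also commonly left to an analysis plan, which is not shown here.

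Much of this stands. The lack of a stated adjustment across outcomes is not a fault in itself. It matters here only because it means the multiplicity text does not rescue the plural reading. The inconsistent labels do not go away, however. The sample size paragraph itself moves from fasting insulin to insulin sensitivity, and an analysis plan cannot make conflicting published statements agree.

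Three stronger readings are tempting, and the documents do not support them.

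- *The false-positive rate on the primary objective is uncontrolled.* That is true only if the set is primary. On the singular reading it is 5%.
- *The plan is to claim success on whichever biomarker reaches significance.* No such rule is written anywhere.
- *The error could be as high as 58%.* Adding two iAUCs, the Matsuda index and three HOMA-2 indices gives 17 outcomes, and 1 − 0.95^17 = 0.582. These indices are built from the same glucose and insulin values as outcomes already counted, so independence is impossible. At assumed correlations of 0.8 to 0.3, the figure for 17 is 21% to 49%.

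**Conclusion.** The inconsistency is in the text and should be corrected. Its statistical size is conditional. The error rate is 5% if fasting insulin alone is primary. It is about 18% to 38% for the 11 Table 1 analytes if the set is primary, with 43% as the independence reference. Even the lowest of these is more than three times the nominal level (0.181 / 0.05 = 3.6).

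The range rests on three assumptions: the count of 11, a common correlation between 0.3 and 0.8, and the reading of the Holm sentence as applying to the post hoc t tests. The first two affect the number. None of them affects the finding that the sections disagree. Because one outcome is already named and sized, this is a should-fix point rather than a fatal one.

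**What to change.** Make the abstract, Objectives, sample size section and Discussion agree: fasting serum insulin is the single primary outcome. Test it once at two-sided 5% by the between-group comparison of change. This can be the group by day interaction already planned, or the follow-up value adjusted for baseline. Replace the reference to insulin sensitivity in the sample size paragraph.

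Label all other biomarkers secondary or exploratory. Then either apply Holm across a list of key secondary outcomes named in advance, or report them as estimates with 95% confidence intervals and no confirmatory claim. The choice of list belongs to the investigators. The Holm adjustment of the post hoc t tests may stay.

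The cost is wording, and fewer outcomes that can support a confirmatory claim. The target of 24 is not changed by this. Whether 24 gives adequate power for a between-group test is a separate question, since the nine comes from a within-group calculation. Timing is favourable: apart from haematology, the blood variables are to be assayed in one batch after the last participant finishes, and the article reports 21 of 24 recruited. The primary outcome could therefore be fixed before any insulin result from that batch exists.

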**Discussion:**

This study will explore the feasibility of home-based moderate-intensity exercise and ascertain its impact on metabolic and cardiovascular health in comparison to a lifestyle maintenance CON group. Findings from this study may help to inform new evidence-based physical activity guidelines and also help to elucidate the physiological mechanisms whereby exercise might exert beneficial effects in persons with chronic SCI. The results will also act as a scientific platform for further intervention studies in other diverse and at-risk populations.

**Trial registration:**

International Standard Randomised Controlled Trial Number: ISRCTN57096451. Registered on 11 July 2014.

## Background

A spinal cord injury (SCI) is a significant life-changing event which has wide-ranging implications for multiple physiological systems. There are no reliable estimates of the global prevalence of SCI, perhaps reflecting the need for improvements in international medical standards and guidelines for reporting SCI. Over the past 60 years there has been a worldwide improvement in the acute survival of patients with traumatic SCI through the possibility of rapid transportation to a specialised unit, medical treatment advancements and improved rehabilitation [1]. As a consequence there has been a shift in focus from acute life support medicine, to addressing other secondary health complications and comorbidities associated with ageing with paralysis [2, 3]. Consequently the long-term demands on medical and support resources are high. A recent systematic review examining survival worldwide after SCI concluded that overall mortality in SCI is up to three times higher than in the general population [4]. Evidence now suggests that cardiovascular disease (CVD) is the leading cause of mortality in individuals with chronic SCI [5]. Besides CVD, epidemiological studies have also revealed the incidence of type-2 diabetes mellitus (T2DM) to be high in individuals with SCI [6–8]. Indeed, it has been suggested that adults with SCI are four times more likely to develop T2DM than non-disabled controls [9].

The contribution of regular physical activity (PA) to reduce the risk of these chronic diseases is well documented and broadly accepted in the non-disabled population [10, 11]. In individuals with SCI, involvement in sports and recreation is often restricted by the loss of voluntary motor control, as well as autonomic dysfunction and early onset of skeletal muscle fatigue [12–14]. There are also numerous psychosocial and environmental barriers: reduced self-esteem, lack of accessible facilities, unaffordable equipment, fear of injury and/or excessive parental or care protection, which have all been cited as barriers to engagement in PA [15–18]. It is likely that the adoption of a more sedentary lifestyle [19–21], in conjunction with reduced physical function [22], and adverse changes in body composition [23, 24] (e.g. lower limb skeletal muscle atrophy [25, 26]) after SCI, contribute to the increased morbidity and mortality associated with this population.

There is convincing evidence to suggest that component risks for the development of metabolic syndrome occur at a heightened frequency in individuals with SCI; specifically, increased central obesity [27–29], impaired fasting glucose/T2DM [30, 31] and dyslipidaemia [32]. The accumulation of excess adiposity is thought to be associated with a sustained positive energy balance secondary to reductions in resting metabolic rate and physical activity energy expenditure. This is associated with local and systemic inflammation, with studies demonstrating a two to threefold increase in the levels of circulating inflammatory markers in persons with SCI compared to non-disabled persons [33–35]. Although elevated chronic inflammation is not formally included among evidence-based metabolic syndrome components, its role in the development of atherosclerosis has been extensively characterised [36–38]. Although it was previously thought that adipose tissue was simply a store for energy, this dynamic tissue is now recognised as an endocrine organ [39–41]. Adipose tissue secretes a number of hormones, collectively termed ‘adipokines’, which play a key role in regulating glucose metabolism and insulin sensitivity, as well as governing aspects of immune function and a variety of other physiological processes. Indeed, the expression of many adipokines is markedly dysregulated with excess adiposity [42] and in individuals with SCI [43, 44]. Although a causal link has not been robustly confirmed, several aspects of immune function are also impaired in sedentary, overweight and obese individuals [45–49] and it is possible that these findings may generalise to individuals with SCI [50].

### The impact of physical activity on health in persons with spinal cord injury

Various biological mechanisms, integral in the maintenance of metabolic control, are influenced by physical inactivity and have been implicated in the progression of certain chronic diseases [51]. To date, cross-sectional evidence has been used to inform PA guidelines for individuals with SCI. These disability-specific guidelines [52], developed as part of the Study of Health and Activity in People with Spinal Cord Injury (SHAPE SCI) [53, 54], propose that at least 20 minutes of moderate- to vigorous-intensity aerobic activity should be undertaken twice a week by people with SCI. These guidelines were developed through a systematic and critical appraisal of research to date, which was then deliberated by a multidisciplinary expert panel to assess the quality of the evidence. The comprehensive systematic review to compile this evidence indicated that most studies informing these guidelines were of poor quality and focused solely on physical capacity and muscular strength [54]. Therefore, there is a lack of empirical evidence regarding the most appropriate dose of exercise or physical activity parameters (e.g. frequency, duration) for improving metabolic health in this population.

The current literature on PA research for individuals with SCI has recently been systematically classified [55]. Most studies between 2000 and 2012 have been categorised as either: phase 1 (linking PA and health outcomes); phase 2 (validating or developing PA monitors) or; phase 3 (identifying factors influencing behaviour or examining theories of behaviour change). Such categorisation implies that this field is in the early stages of development and research should now focus on phase 4 (evaluating interventions) and phase 5 (disseminating health promotion policies and translating research into practice). Due to the inconsistent findings across studies, concluded via a systematic review requested by the Consortium for Spinal Cord Medicine [56], it would appear that current evidence is insufficient to determine whether exercise improves carbohydrate and lipid metabolism disorders among adults with SCI. However, previous studies have demonstrated that arm-crank exercise improves lipid profiles [57], inflammatory biomarkers [58] and fasting insulin concentrations [59] with interventions ranging from 12 to 16 weeks in duration. It is possible that inconsistencies in the current literature may be caused by considerable heterogeneity in study participants, the type of exercise programme and/or the outcome measures examined. Here we describe the study design for a randomised controlled trial (RCT) with a homogeneous cohort, examining a variety of outcome measures not simply confined to physical capacity, that will contribute towards our understanding of how a home-based upper body exercise intervention might impact metabolic, cardiovascular and immunological health in individuals with SCI: the HOMEX-SCI study.

